## Abstract

**Background:**

Acute gastroenteritis (AGE) is one of the most common diseases among children. Oral rehydration therapy is the key treatment. However, despite proven efficacy, it remains underused. This is because oral rehydration solution neither reduces the frequency of bowel movements and fluid loss nor shortens the duration of illness. Hence, there is interest in adjunctive treatments. According to the 2014 guidelines developed by the European Society for Paediatric Gastroenterology, Hepatology and Nutrition, the use of the following probiotics may be considered in the management of children with AGE in addition to rehydration therapy: *Lactobacillus rhamnosus* GG (low quality of evidence; strong recommendation) and *Saccharomyces boulardii* (low quality of evidence; strong recommendation). Less compelling evidence is available for *Lactobacillus reuteri* DSM 17938 (very low quality of evidence; weak recommendation).

**Objective:**

Considering that evidence on *L reuteri* remains limited, the goal of the study is to assess the effectiveness of *L reuteri* DSM 17938 in the treatment of AGE in children. Children vaccinated and not vaccinated against rotavirus will be evaluated separately.

**Methods:**

This will be a double-blind, placebo-controlled, randomized trial. Children between 1 and 60 months of age with AGE, defined as a change in stool consistency to loose or liquid form (according to the Bristol Stool Form scale or Amsterdam Stool Form scale) and/or an increase in the frequency of evacuations (typically ≥3 in 24 h) lasting for no longer than 5 days, will be recruited. A total of 72 children will receive either *L reuteri* DSM 17938 at a dose of 2×10^8^colony-forming units twice daily or matching placebo for 5 consecutive days. A similar sample size for rotavirus vaccinated and nonvaccinated children is planned. The primary outcome measure is the duration of diarrhea. Two separate studies and reports for rotavirus vaccinated and nonvaccinated children are planned.

**Results:**

The recruitment started in January 2017 and is planned to be finalized in June 2018 for rotavirus nonvaccinated children. The recruitment of rotavirus-vaccinated children may be slower due to a relatively low coverage rate in Poland. Data analysis and submission to a peer-reviewed journal is expected within 3 months after completion of the study.

**Conclusion:**

This study will add to current knowledge on the efficacy of *L reuteri* DSM 17938 for the management of AGE.

**Trial registration:**

ClinicalTrials.gov NCT02989350; https://clinicaltrials.gov/ct2/show/NCT02989350 (Archived by WebCite at http://www.webcitation.org/6slOFkyTH)

## Introduction

Acute gastroenteritis (AGE) is one of the most common diseases among children. Generally, this is a self-limited illness lasting 5 to 7 days, and thus, the main aim of treatment is to prevent dehydration, metabolic acidosis, and electrolyte disturbances. In the vast majority of cases of AGE with mild or moderate dehydration, this can be achieved with oral rehydration solutions. Despite the proven efficacy of oral rehydration, it remains underused [1]. The main reason for this is that an oral rehydration solution neither reduces the frequency of bowel movements and fluid loss nor shortens the duration of illness, which decreases its acceptance and prompts interest in adjunctive treatments.

In 2014, the European Society for Paediatric Gastroenterology, Hepatology and Nutrition (ESPGHAN) provided recommendations for the use of probiotics for the treatment of AGE in previously healthy infants and children based on a systematic review. The use of the following probiotics may be considered in the management of children with AGE in addition to rehydration therapy: *Lactobacillus rhamnosus* GG (low quality of evidence; strong recommendation) and *Saccharomyces boulardii* (low quality of evidence; strong recommendation). Less compelling evidence is available for *Lactobacillus reuteri* DSM 17938 (very low quality of evidence; weak recommendation) [2,3].

*L reuteri* is named after Gerhard Reuter, a German microbiologist [4]. Among a number of *L reuteri* strains, *L reuteri* DSM 17938 is probably the best studied. *L reuteri* DSM 17938 is the daughter strain of *L reuteri* ATCC 55730. The latter was originally isolated from the breast milk of a Peruvian mother, and it may be present in normal humans on the mucosa of the gastric corpus and antrum, duodenum, and ileum [4,5]. As *L reuteri* ATCC 55730 was found to carry potentially transferable resistance traits for tetracycline and lincomycin, it was replaced by *L reuteri* DSM 17938, a strain without unwanted plasmid-borne resistance [6]. Like other *L reuteri* strains, *L reuteri* DSM 17938 has several different types of mechanisms of action. One of the best-documented mechanisms is its antimicrobial activity. *L reuteri* strains produce reuterin, a broad-spectrum antibacterial substance [7,8], which is capable of inhibiting the growth of a wide spectrum of microorganisms such as Gram-positive or negative bacteria, yeast, fungi, or parasites [9]. *L reuteri* strains may also regulate immune responses [10-12].

The clinical efficacy of *L reuteri* DSM 17938 has been studied in a number of clinical trials, including studies aimed at the assessment of *L reuteri* DSM 17938 in the management of AGE.

A 2012 study by Francavilla et al [13] was carried out in 74 children with acute diarrhea randomized to receive *L reuteri* DSM 17938 (at a dose of 4×10^8^colony-forming units [CFU]) or placebo for 7 days. Compared with the placebo group, in the *L reuteri* group there was a significant reduction in the duration of diarrhea (3.3 [SD 2.1] vs 2.1 [SD 1.7] days, respectively; *P*<.03), the risk of watery diarrhea on day 2 (81% vs 55%, respectively, *P*<.02) and on day 3, 73% vs 46%, respectively, *P*<.03), and the risk of relapse of diarrhea (42% vs 15%; respectively, *P*<.03). There was not a significant difference in hospital stay between the groups.

A 2014 multicenter, randomized, single-blind clinical trial by Dinleyici et al [14] was performed in 127 hospitalized children with AGE lasting 12 to 72 hours. Conventional therapy plus the administration of *L reuteri* DSM 17938 at a dose 1×10^8^CFU for 5 days compared with conventional therapy alone (control group) reduced the duration of diarrhea (70.7 [SD 26.1] vs 103.8 [SD 28.47] hours, respectively; *P*<.001), increased the number of diarrhea-free children after 24 and 48 hours (50% vs 5%, respectively, *P*<.001) and 72 hours (69% vs 11%, respectively, *P*<.001), and reduced the hospital stay (4.3 [SD 1.3] days vs 5.46 [SD 1.77] days, respectively, *P*<.001).

A 2015 trial by the same authors performed in 64 outpatient children with acute infectious diarrhea found that compared with oral rehydration therapy alone (control group), the additional administration of *L reuteri* at a dose 1×10^8^CFU for 5 days significantly reduced the duration of diarrhea (74.3 [SD 15.3] hours vs 60.4 [SD 24.5] hours, respectively, *P*<.05). The percentage of children with diarrhea after 48 hours was lower in the *L reuteri* group than the control group (13/29 vs 27/31, respectively; relative risk [RR] 0.51, 95% CI 0.34 to 0.79, *P*<.01). From the 72nd hour of the intervention onward, there was no difference between the 2 groups in the percentage of children with diarrhea [15].

A 2015 meta-analysis of these 3 randomized controlled trials (n=256) found that compared with placebo or no treatment, *L reuteri* DSM 17938 administration significantly reduced the duration of diarrhea (mean difference [MD] –24.82 hours, 95% CI –38.8 to –10.8) and increased the chance of cure on day 1 (RR 11.3, 95% CI 2.2 to 59) and day 2 (RR 4.54, 95% CI 2.0 to 10.2) [16]. However, heterogeneity and wide confidence intervals call for caution in interpreting the results. To the best of our knowledge, there are no data on the use of probiotics use in rotavirus-vaccinated children with AGE.

More studies are needed to establish the efficacy of *L reuteri* DSM 17938 in the management of AGE in children. We aim to conduct a well-designed study with sufficient power, an adequate follow-up period, and relevant clinical end points. The study will be led by a team experienced in performing clinical trials in children with AGE [17,18] and follow the same protocol as one of our recent trials on AGE [19].

The objective of this study is to assess the effectiveness of *L reuteri* DSM 17938 in the treatment of AGE in children. Children vaccinated and not vaccinated against rotavirus will be evaluated separately.

## Methods

### Study Design

This study is designed as a randomized, double-blinded, placebo-controlled trial with 1:1 allocation, and it is described in more detail in the subsequent sections. The trial was registered at ClinicalTrials.gov [NCT02989350], and any important changes in the protocol will be implemented there.

### Ethics and Dissemination

The Ethical Committee of the Lower Silesia Medical Chamber issued approval for the study before recruitment commenced. Verbal and written information regarding informed consent will be presented to the caregivers. Any modifications to the protocol that may affect the conduct of the study will be presented to the Ethical Committee. The full protocol will be available freely due to open-access publication. The findings of this randomized controlled trial will be submitted to a peer-reviewed journal. Abstracts will be submitted to relevant national and international conferences. The need for separate reporting of data on rotavirus-vaccinated and nonvaccinated populations is foreseen. The Ethics Committee did not require auditing for this study.

### Setting and Participants

The recruitment will take place in the emergency room and the Department of Paediatrics of the St Hedwig of Silesia Hospital in Trzebnica, Poland. However, inclusion of outpatients and involvement of other recruiting sites are under consideration provided the study staff is experienced, adequately trained, and competent in conducting clinical trials. The start of the recruitment is planned in January 2017, and it should be completed within the following 2 years. Participants will be randomized after their first visit to the emergency room or after admission to the hospital. Caregivers will receive oral and written information on the study. Written informed consent will by obtained by physicians involved in the study. See Textbox 1 for selection criteria.

### Interventions

The intervention under investigation is *L reuteri* DSM 17938 *.* The placebo drops consist of a mixture of pharmaceutical grade medium chain triglycerides and sunflower oil together with pharmaceutical grade silicon dioxide to give the product the correct rheological properties. The formulation is identical to the active product but without  *L reuteri* DSM 17938. In our trial, we choose to use a placebo for a comparator, as it is widely regarded as the gold standard for testing the efficacy of new treatments [20,21].

The study products (*L reuteri* DSM 17938 and placebo) will be manufactured and supplied by BioGaia as bottle with drops, free of charge. The manufacturer will have no role in the conception, protocol development, design, or conduct of the study or in the analysis or interpretation of the data.

The dose of *L reuteri* DSM 17938 will be 2×10^8^CFU. Both *L reuteri* DSM 17938 and placebo will be taken orally, 5 drops twice daily for a consecutive 5 days. Caregivers will be instructed to administer the study products at the same time of the day. If needed, discontinuation or modification of the treatment may be considered at the discretion of the physician.

Table 1 presents a timetable of activities planned during the study. For initial rehydration, all children will be treated according to the 2014 ESPGHAN recommendations (fast oral rehydration over 3 to 4 hours by mouth or via nasogastric tube with the recommended hypotonic solution) [3]. After all signs of dehydration have disappeared, oral rehydration solution will be given for ongoing losses until the diarrhea stops. Rapid reintroduction of the previous diet after successful rehydration will be recommended.

Selection criteria.Inclusion criteria:Acute gastroenteritis defined as a change in stool consistency to loose or liquid form (according to the Bristol Stool Form scale or in the case of infants, the Amsterdam Stool Form scale) and/or an increase in the frequency of evacuations (typically ≥3 in 24 hours) lasting for no longer than 5 daysAged older than 1 month and younger than 60 monthsCaregiver must provide written informed consentExclusion criteria:Use of antibiotics within 2 weeks prior to enrollmentUse of gelatine tannate, diosmectite, probiotics, racecadotril, or zinc (including zinc-containing oral rehydration solution) within 1 week prior to enrollment (a single dose is allowed)Breastfeeding (>50%).Chronic diarrheal gastrointestinal disease (eg, inflammatory bowel disease, cystic fibrosis, celiac disease, food allergy)ImmunodeficiencyMalnutrition (weight/height/length under 3rd percentile) (World Health Organization Child Growth Standards will be used) [20]

**Table 1 table1:** Timetable of activities planned during the study.

Activities	Days							
	1	2	3	4	5	6	7	8
Inclusion/exclusion criteria	x							
Informed consent	x							
Enrollment	x							
Randomization	x							
Stool sample taken	x							
Intervention	x	x	x	x	x			
Follow-up						x	x	x
Return of diary								x
Concomitant medication	x	x	x	x	x	x	x	x
Adverse events	x	x	x	x	x	x	x	x

After rechecking the inclusion and exclusion criteria, participants will be assigned into 1 of 2 groups (experimental or control). Caregivers will receive a diary of symptoms to record the number of stools and stool consistency during the intervention (including recording of the timing of stools); Bristol Stool Form (BSF) and Amsterdam Stool Form (ASF) scales will be provided. Additionally, caregivers will be asked to write down any adverse events and concomitant medication during the intervention period. In line with current ESPGHAN guidelines [3], children presenting with AGE do not require routine etiological investigation; however, before the first dose of study products, a stool sample will be taken to determine the rotavirus etiology of the diarrhea with a standard immunoassay method. More specific microbiological investigations with standard stool cultures will be performed only if needed [3]. At any time, caregivers will have the right to withdraw the participating child from the study; they will be not obliged to give reasons for this decision, and there will be no effect on subsequent physician and/or institutional medical care.

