### Follow-Up

All study participants will be followed up for the duration of the intervention (5 days) and then for an additional 3 days or until the cessation of diarrhea.

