### Outcomes

The primary outcome will be the duration of diarrhea, defined as the time until the normalization of stool consistency according to the BSF or ASF scale (in BSF scale, numbers 1, 2, 3, 4, and 5; in ASF scale, letters B or C) or the time until the normalization of the number of stools (compared with the period before the onset of diarrhea) and the presence of normal stools for 48 hours.

Secondary outcomes will include:

Need for intravenous rehydrationDuration of intravenous rehydrationNeed for hospitalization of outpatientsNumber of watery stools per dayVomitingRecurrence of diarrhea (48 hours after intervention)Severity of diarrhea according to Vesikari scale [22]Use of concomitant medicationsAdverse events

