### Compliance

The caregivers will be asked to bring the remaining study product and diary to the study site at the end of the intervention period. Compliance with the study protocol will be checked by measuring the volume left unused. Based on previously published trials, it seems appropriate to consider those participants receiving <75% of the recommended doses as noncompliant.

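### The text has the stool diary kept during, and returned after, the 5 treatment days, while Table 1 has it returned on day 8; followed literally, the text leaves later primary-outcome events unconfirmed

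*Protocol article*

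**What the plan says.** Five places in the protocol article bear on how long stools are recorded.

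- **Interventions, diary.** Caregivers receive a "diary of symptoms to record the number of stools and stool consistency during the intervention", including the timing of stools. In addition, "caregivers will be asked to write down any adverse events and concomitant medication during the intervention period". The product is given as "5 drops twice daily for a consecutive 5 days".
- **Compliance.** Caregivers are to "bring the remaining study product and diary to the study site at the end of the intervention period".
- **Table 1.** The row "Return of diary" has one mark, on day 8. The intervention is marked on days 1-5 and follow-up on days 6-8. Concomitant medication and adverse events are marked on all eight days.
- **Follow-Up.** Children are "followed up for the duration of the intervention (5 days) and then for an additional 3 days or until the cessation of diarrhea".
- **Outcomes.** Duration of diarrhea runs to normalization of stool consistency or of stool number "and the presence of normal stools for 48 hours". A secondary outcome is recurrence of diarrhea, tied to 48 hours after the intervention.

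**The concern.** The diary is the only source of stool timing and consistency that the article describes, and the article gives two incompatible times for its return. Interventions and Compliance agree with each other on a record covering the 5 treatment days. Table 1, Follow-Up and both outcomes need a record that continues afterwards, yet nowhere are caregivers told to record stools on days 6-8.

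A site that follows the text would have no diary entries for the recurrence outcome. It could not confirm the 48 h of normal stools for any child whose diarrhea stops late in the treatment period or after it. Statistical Analysis includes children for whom outcomes are available, so a child without a confirmed end may drop out of the primary comparison. Late-resolving children are expected more often on placebo if the product works, so the loss would differ between arms.

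**Working it through.** **Inputs**
- Treatment period: 5 days = 120 h (Interventions, Table 1).
- Last day in Table 1: day 8 = 192 h.
- Confirmation period: 48 h (Outcomes), taken to apply to both branches of the definition.
- Durations in the three cited trials (Introduction), control vs active: 127-child hospitalized trial 103.8 (SD 28.47) vs 70.7 (SD 26.1) h; 74-child placebo-controlled trial 3.3 (SD 2.1) vs 2.1 (SD 1.7) days, i.e. 79.2 (50.4) vs 50.4 (40.8) h; 64-child outpatient trial 74.3 (15.3) vs 60.4 (24.5) h.

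**Step 1: the plan's own figure.** A 24 h difference with SD 24 h, two-sided alpha 0.01 and 90% power gives 30 per arm by the normal approximation. This is the 60 evaluable children in Power Calculation. The diary point does not depend on it, but 60 is the number that needs a primary outcome.

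**Step 2: latest cessation that can be confirmed** = end of diary - 48 h.
- Diary ends with treatment: 120 - 48 = **72 h**.
- Diary kept to day 8: 192 - 48 = **144 h**.

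**Step 3: share of children beyond each limit**, P(X > c) = 1 - Φ((c - mean)/SD). For example, hospitalized controls at 72 h: (72 - 103.8)/28.47 = -1.117, giving 0.868.

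| Trial | Beyond 72 h, control / active | Beyond 144 h, control / active |
|---|---|---|
| Hospitalized | 86.8% / 48.0% | 7.9% / 0.2% |
| Placebo-controlled | 55.7% / 29.8% | 9.9% / 1.1% |
| Outpatient | 56.0% / 31.8% | 0.0% / 0.0% |

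Averaged over two equal arms, the share beyond 72 h is (86.8 + 48.0)/2 = 67%, (55.7 + 29.8)/2 = 43% and (56.0 + 31.8)/2 = 44%. Power Calculation allows for about 20% loss.

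**Step 4: effect on the mean difference.** If unconfirmed episodes are dropped, each arm's mean becomes mean - SD × φ(z)/Φ(z), with z = (c - mean)/SD. If every episode is kept and durations are capped at the 120 h diary end, the mean is mean × Φ(z) - SD × φ(z) + 120 × (1 - Φ(z)), with z taken at 120 h.

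| Trial | True difference | Dropped beyond 72 h | Capped at 120 h | Dropped beyond 144 h |
|---|---|---|---|---|
| Hospitalized | 33.1 h | 57.7 - 50.7 = 7.0 h | 28.3 h | 28.8 h |
| Placebo-controlled | 28.8 h | 34.3 - 30.2 = 4.1 h | 23.6 h | 20.2 h |
| Outpatient | 13.9 h | 60.6 - 47.6 = 13.0 h | 14.0 h | 13.9 h |

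**Step 5: upper bound.** If the 5 to 7 day mean in Power Calculation, with SD 24 h, counted from first dose, 98-100% would exceed 72 h and 16-84% would exceed 144 h. That mean probably includes illness before entry, which may last up to 5 days, so this is an extreme.

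**The case against.** The strongest reply is that the document as a whole supports a record to day 8. Table 1 schedules diary return then, follow-up is planned for days 6-8, and returning a diary on day 8 makes little sense if entries stop on day 5. The text does not say that recording happens only during treatment. Some children are inpatients, case report forms and outcome assessors are mentioned, and an article may leave the capture of follow-up data to the full protocol.

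Much of this stands. A reader might infer that cessation after 72 h can never be confirmed in this trial. The documents do not support that: on Table 1's schedule the limit is about 144 h, and few children pass it. A reader might also infer that the trial is bound to be strongly biased towards no effect. That does not follow either. The article does not say how an unconfirmed episode is scored, capping at the diary end keeps most of the difference, and the outpatient trial shows almost no shrinkage even when such episodes are dropped. The 72 h limit also rests on applying the 48 h criterion to both branches, which the sentence in Outcomes leaves unclear. Finally, the normal model is crude: for the placebo-controlled trial it puts about 6% of control and 11% of active durations below zero.

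The contradiction itself survives. This is not detail left out for brevity: the article states two return times for its main outcome instrument, and the two passages that instruct caregivers are the ones with the short window.

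**Conclusion.** The point holds as an internal contradiction with a possible cost to the primary outcome. Interventions and Compliance conflict with Table 1, and they do not cover the period needed by Follow-Up, the 48 h criterion or the recurrence outcome.

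The size depends on which instruction sites follow. Under the text, 56-87% of controls and 30-48% of treated children would stop too late to be confirmed by the diary. Under Table 1 these shares are 0-10% and at most about 1%. The effect on the estimated difference under the text ranges from negligible to severe if such episodes are dropped, and is smaller if they are scored at the diary end. These figures are illustrations. They assume normal durations counted from enrolment, a diary starting at first dose, no other source of stool data, and a 48 h criterion that applies to both branches.

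Follow-Up adds a smaller ambiguity: its two end points are joined by an unqualified alternative, and it does not say whether cessation includes the 48 h of confirmation.

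**What to change.** - In Interventions, have the diary (stools, adverse events and concomitant medication) kept daily to day 8 or, if later, until 48 h of normal stools have been recorded.
- In Compliance, have the diary returned at that point, in line with Table 1. Return of unused product can keep its own date.
- In Follow-Up, state that follow-up runs to the later of the two end points and includes the 48 h of confirmation.

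The cost is a wording change and a few more diary days per family; Table 1 already plans the day-8 return. The change concerns data collection only. Recruitment has started, so it should reach sites promptly, because stools not recorded at the time cannot be reliably reconstructed.
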